**ii. Measurements and monitoring by the un-blinded investigator**

- a. At t= 40, 45, 50, 55, 60, 65, 70, 75, 80 record the time and SpO2
- b. Monitor the SpO2 and if the nasal cannulae oxygen flow is changed, document the time and new oxygen flow

### iii. Measurements and monitoring by the blinded investigator

- a. At t= 40, 45, 50, 55, 60, 65, 70, 75, 80 record the time, PtCO2 and heart rate.

[figure not shown]

\*From Time 0 only.

#Nasal cannulae oxygen delivery will be stopped during this time. It will be recommenced at the time of the nebuliser finishing at the same rate as immediately before the nebuliser was given.

\*\* Baseline measures are: Time; SpO2; oxygen flow via nasal cannulae, if any; PtCO2 and HR

## Minimum time period of 15 minutes prior to capillary blood gas

\*\*\* Oxygen delivered at fixed flow (see section F.i.)

HR: Heart rate,  $P_{\text{capCO}_2}$ : Capillary partial pressure of carbon dioxide,  $P_t\text{CO}_2$ : Transcutaneous partial pressure of carbon dioxide,  $\text{SpO}_2$ : oxygen saturations

---

## 7. Outcome variables

### A. COMPARATOR GROUPS

Outcome variables will be compared between the air versus oxygen driven nebuliser regimens.

### B. OUTCOME MEASUREMENTS

Capillary blood gas samples (CBG) will measure  $p\text{CO}_2$  ( $P_{\text{capCO}_2}$ ) and pH. The samples will be collected in capillary tubes and analysed at the Wellington Regional Hospital or Hutt Valley Hospital laboratory. The transcutaneous monitor will be placed on the participant's earlobe (or backup sites as listed above) to measure transcutaneous  $\text{PaCO}_2$  ( $P_t\text{CO}_2$ ), oxygen saturation ( $\text{StO}_2$ ) and heart rate. Finger pulse oximetry will measure oxygen saturation ( $\text{SpO}_2$ ).

### C. PRIMARY OUTCOME VARIABLE

- i.  $P_t\text{CO}_2$  at completion of the second nebulisation (at  $t=35\text{min}^*$ ), adjusted for baseline.

\*or the last recorded measurement should the  $t=35$  measurement not be obtained (e.g. study terminated early due to rise in  $P_t\text{CO}_2 \geq 10\text{mmHg}$ ).

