## 4. Randomisation and blinding

### A. RANDOMISATION

Randomisation will be 1:1 via a block randomised (block size 6) computer generated sequence, provided by the study statistician independent of recruitment and assessment of participants. The allocated intervention will be stored in an opaque sealed envelope and opened at the time of randomisation by the un-blinded investigator.

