#### **iv. Regimen monitoring and measurements by the un-blinded investigator**

- a. At t= 5, 6, 10, 15, 20, 25, 26, 30, 35 record the time and SpO2.
- b. Monitor the SpO2 and if the nasal cannulae oxygen flow is changed, document the time and new oxygen flow (air driven regimen only).
- c. Document the time the nebulised medication canister becomes empty.
- d. As close as possible prior to the completion of the second nebuliser at t=35 minutes, a CBG measurement will be taken, as per the SOP. On visualisation of blood entering the capillary tube un-blinded investigator ask blinded investigator to record the time and PtCO2. The CBG will be taken whilst the air/oxygen-driven nebuliser is still in place: if the investigator runs into technical difficulties (for example, slow blood flow when collecting CBG sample), then the nebuliser shall be removed at no later than t=37 minutes.

NOTE: The t=20 measure is to occur immediately prior to initiation of the 2nd nebuliser and the t= 15 and t=35 measures are to occur immediately prior to cessation of nebuliser delivery. In the event of a PtCO2 rise of ≥10mmHg

from baseline whereby a nebuliser has to be terminated early, the CBG measurement will be taken at this time-point. The top priority if this occurs is removal of oxygen and clinical assessment of the patient. CBG MUST OCCUR AFTER THIS.

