**v. Regimen monitoring and measurements by the blinded investigator**

- a. At t= 5, 6, 10, 15, 20, 25, 26, 30, 35 record the time, PtCO2 and heart rate.
- b. Continuously monitor PtCO2, and should it increase by  $\geq 10$ mmHg from baseline measure (t=0), indicate this to the un-blinded investigator so they can terminate the regimen intervention.
- c. Record the time and PtCO2 during arterialised earlobe blood gas sampling, as prompted by the un-blinded investigator.

NOTE: The t=20 measure is to occur immediately prior to initiation of the 2nd nebuliser and the t= 15 and t=35 measures are to occur immediately prior to cessation of nebuliser delivery

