## **10. Power and Statistical Methods**

A difference in  $PaCO_2$  of 4 mmHg represents a physiologically significant change.  
 In our controlled study of oxygen versus air driven nebulisers in stable COPD the standard deviation of  $P_tCO_2$  was 5.5. With 90% power and alpha of 5% this requires a total of 82 patients to detect a 4 mmHg difference. We anticipate a drop-out rate of <10% so our target recruitment is 90 patients. Analysis will be by intention to treat. Participants recruited will be stratified in to groups that were receiving oxygen immediately prior to randomisation or those that were not. Our primary analysis is ANCOVA with  $P_tCO_2$  as the response variable, and randomised treatment and baseline  $P_tCO_2$  as co-variables. For other continuous outcome variables we will also use similar ANCOVA. Exploratory analyses for  $P_tCO_2$ , heart rate and  $SpO_2$  taken at five minute intervals will be presented graphically and analysed by mixed linear models.

---

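### When a participant is stopped for a PtCO2 rise of 10 mmHg or more, the protocol does not require the triggering value to be recorded, so the last-recorded fallback can understate the primary outcome

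*Protocol*

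**What the plan says.** - **Primary outcome (Protocol 7.C).** PtCO2 at completion of the second nebulisation, t=35, adjusted for baseline, "or the last recorded measurement should the" t=35 value not be obtained. The example given is an early stop for a rise of 10 mmHg or more.
- **What is written down (6.E.v).** The blinded investigator's schedule is: "At t= 5, 6, 10, 15, 20, 25, 26, 30, 35 record the time, PtCO 2 and heart rate". One further reading is taken "during arterialised earlobe blood gas sampling, as prompted by the un-blinded investigator".
- **What happens at the trigger (6.E.v).** PtCO2 is watched continuously. If it rises by 10 mmHg or more from t=0, the blinded investigator is to "indicate this to the un-blinded investigator so they can terminate the regimen intervention". No instruction to record the value accompanies this, and the list of that investigator's roles in 4.B.v adds none.
- **The CBG at an early stop (6.E.iv).** The note first says "the CBG measurement will be taken at this time-point", then: "The top priority if this occurs is removal of oxygen and clinical assessment of the patient. CBG MUST OCCUR AFTER THIS".
- **Related secondary outcomes (7.D).** Item v is the greatest PtCO2 change at recorded time points up to t=35 with the nebuliser in place. Item vii counts terminations for a rise of 10 mmHg or more.

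**The concern.** The fallback was written with the participants who have the largest CO2 rises in mind, yet the recording instructions do not secure the reading that shows the rise. If the value that enters the ANCOVA is lower than the one that caused the stop, the primary outcome is understated in those participants. The trial's first hypothesis expects such rises with oxygen-driven nebulisation. If stops do fall mainly in that arm, the error pulls the treatment difference toward zero and hides part of the harm the trial is designed to detect.

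The secondary outcomes can also disagree. Item v can show a greatest change below 10 mmHg for a participant whom item vii counts as a termination for a rise of at least 10 mmHg.

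An analysis plan cannot repair this later, because a value not written down at the bedside may not be recoverable.

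**Working it through.** **Step 1. Which reading can be the last recorded one?** Suppose the criterion is met at some time before t=35.

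| Case | Last recorded PtCO2 | Relation to the trigger value |
|---|---|---|
| Trigger falls on a scheduled time | That scheduled reading | Captured, no loss |
| Trigger between scheduled times, CBG-paired reading missed or not counted | The preceding scheduled reading | Below baseline +10 by construction, since an earlier +10 would already have triggered the stop |
| Trigger between scheduled times, CBG-paired reading counted | A reading after oxygen removal and clinical assessment | Probably lower, depending on a delay the protocol does not state |

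The gaps between scheduled readings are 1 to 5 minutes, so a trigger between them is the ordinary case.

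**Step 2. Secondary outcome v.** It is limited to recorded time points with the nebuliser in place, so the reading in the third row does not qualify. In the second and third rows the greatest change is therefore below 10 mmHg, while outcome vii records a rise of at least 10 mmHg.

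**Step 3. Reproduce the planned sample size.** Section 10 states: "With 90% power and alpha of 5% this requires a total of 82 patients to detect a 4 mmHg difference", with SD 5.5. Allocation is equal (4.A: "Randomisation will be 1:1 via a block randomised (block size 6) computer generated sequence"). Two-sided 5% is assumed, since sidedness is not stated.
- Normal approximation: n per arm = 2 × (5.5/4)² × (1.960 + 1.282)² = 39.7, so 40 per arm and 80 in total.
- Two-sample t-test: 40.7, so 41 per arm and 82 in total. The stated figure reproduces.
- Power with 41 per arm by the t-test: 90.2%.

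**Step 4. Illustrate the effect.** The protocol gives no expected number of stops and no size of understatement, so both are assumptions. All stops are placed in an oxygen arm of 45 (half of 90).

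Difference = 4 − (stops/45) × understatement. Power is from the two-sample t-test with 41 per arm and SD 5.5.

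| Stops | Understatement each (mmHg) | Dilution (mmHg) | Difference (mmHg) | Power |
|---|---|---|---|---|
| 0 | – | 0 | 4.00 | 90% |
| 1 | 3 | 1/45 × 3 = 0.07 | 3.93 | 89% |
| 1 | 8 | 1/45 × 8 = 0.18 | 3.82 | 87% |
| 2 | 3 | 2/45 × 3 = 0.13 | 3.87 | 88% |
| 2 | 8 | 2/45 × 8 = 0.36 | 3.64 | 84% |
| 5 | 3 | 5/45 × 3 = 0.33 | 3.67 | 85% |
| 5 | 8 | 5/45 × 8 = 0.89 | 3.11 | 72% |

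Five is the number of such rises that brings the safety board meeting forward (section 9). It is used only as a scenario.

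**The case against.** **Which reading counts.** Section 6.E.iv does provide a reading for early stops, the one paired with the CBG, and states no delay. Taken promptly, it could be close to the trigger value. A trigger at a scheduled time is captured. Both points stand: understatement is certain only when a pre-trigger reading is carried forward.

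**A stronger reading that the text does not support.** A reader might infer that, if recording continues after the stop, a reading at clock time t=35, long after the oxygen nebuliser came off, becomes the primary value. Section 7.C ties the outcome to completion of the second nebulisation and gives early stopping as an example of t=35 not being obtained. Sections 6.E.iv and 6.E.v place the t=35 measure immediately before nebuliser delivery ceases. Read together, an off-nebuliser reading is not the t=35 measurement. The wording is still loose: 7.C's example speaks of the study ending early, 6.E.v only of the regimen intervention.

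**The size is assumed.** This stands. Five stops is an alarm count over all participants, not a forecast, and the 3 and 8 mmHg figures have no source in the protocol. Step 4 also uses 45 for dilution and 41 for power, and holds the SD at 5.5. Lowering the highest values in one arm also reduces its SD: simulating this with 41 per arm and the five highest values lowered gives power of about 86 to 87% (3 mmHg) and 75 to 76% (8 mmHg). The table slightly overstates the loss in those rows.

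**Direction and lost events.** If stops fall in the oxygen arm, the bias is toward no difference and would not create a false positive, and outcome vii still counts terminations. Both are true. But a trial looking for harm is poorly served by a bias that hides it, and a count of stops does not restore the primary value.

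**Conclusion.** The concern holds in a limited form. The protocol fixes a fallback for participants stopped for a rise of at least 10 mmHg but does not require the value that triggered the stop to be recorded. Unless the trigger falls on a scheduled time, the primary value is either a reading below +10 by construction or an off-gas reading that is probably, not certainly, lower. If stops occur mainly in the oxygen arm, which is the trial's hypothesis rather than a documented rate, the primary difference is biased toward zero.

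The size cannot be known from the protocol. It is minor with one or two stops and a small understatement, and material with about five stops and a large one. A reader might infer that the largest rises are always understated, or that power will fall to about 72%. The text supports neither: the first ignores captured triggers and prompt readings, and the second is the most adverse scenario in Step 4. The change is still worth making before recruitment, because the affected participants are the ones the rule names and an unrecorded value may be lost.

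**What to change.** 1. **Section 6.E.v:** the blinded investigator records time and PtCO2 when the 10 mmHg criterion is met, without delaying the signal.
2. **Section 7.C:** for participants stopped for this reason, the primary value is that recorded trigger value. Later off-nebuliser readings, including one at clock time t=35, count neither as the t=35 nor as the last recorded measurement. Keep the last-recorded rule for t=35 readings missing for other reasons.
3. **Section 7.D, item v:** include the trigger value.
4. **Reconcile wording:** whether the study or only the regimen intervention ends at an early stop (7.C against 6.E.v), and the two statements on CBG timing in the 6.E.iv note. How these are resolved is for the sponsor.

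The cost is one case report form field and a few sentences. The blinded investigator is already watching the number. Sample size, stopping rule and order of patient care do not change.

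The downside is that the measurement time for stopped participants depends on the outcome and their values will sit near +10. That is already partly so under the existing fallback.

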### D. SECONDARY OUTCOME VARIABLES

- i.  $P_{\text{capCO}_2}$  at completion of the second nebulisation (immediately prior to  $t=35\text{min}$ ), adjusted for baseline  $P_{\text{capCO}_2}$ .
- ii. pH at completion of the second nebulisation (immediately prior to  $t=35\text{min}$ ), adjusted for baseline.
- iii.  $P_t\text{CO}_2$  at six minutes after the initiation of the first and second nebulisers ( $t=6\text{min}$  and  $t=26\text{min}$ )
- iv.  $P_t\text{CO}_2$ ,  $\text{SpO}_2$  and heart rate at 5 minute intervals from  $t=0$  to  $t=80\text{min}$

- v. Greatest PtCO2 change from baseline at any of the recorded time points between t=0 and t=35 minutes when the nebuliser is in place.
- vi. Proportion of participants with  $\geq 4$ mmHg (physiologically significant) and  $\geq 8$ mmHg (clinically significant) increase in PcapCO2 or PtCO2 from baseline
- vii. Number of intervention terminations due to a rise in PtCO2  $\geq 10$ mmHg
- viii. The proportion of patients with a reduction in pH of  $\geq 0.06$  from baseline
- ix. Proportion of patients who required initiation of an increase in the flow of oxygen therapy during the regimen and observation periods.

NOTE: PtCO2 measurements recorded and analysed will be the actual (raw) data from the Transcutaneous Monitoring System, but adjustments for 'drift' will also be reported upon.

---

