## **iv. Roles of the un-blinded investigator**

- a. Recording medical history, demographics and obtaining written informed consent (either investigator can do this prior to blinding).
- b. CBG sampling
- c. Randomisation
- d. Administration of the randomised intervention
- e. Recording and monitoring of finger probe SpO2
- f. Increase oxygen therapy if SpO2 <85%.

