## **iii. Regimens**

### Air driven nebuliser regimen

- a. t=0-15 min: 2.5 mg salbutamol by nebulisation, delivered by air at a flow rate of 8L/min
- b. t=15-20 min: Removal of nebuliser mask
- c. t=20-35 min: 2.5 mg salbutamol by nebulisation, delivered by air at a flow rate of 8L/min.

The nebuliser is to continue running for the entire 15 minutes at t=0-15 min and t=20-35 min, even if the bronchodilator medication has dissipated.

Oxygen therapy is to be continued to be titrated by the un-blinded investigator using nasal cannulae (worn under the nebuliser mask at 0-15 and 20-35 min). Note that if the patient was not receiving oxygen before the intervention (was breathing room air) this will continue unless the oxygen saturations drop to <85%. If this occurs the nebuliser mask will be removed, nasal prongs attached and oxygen given before reattaching the nebuliser mask. If this does happen it will be recorded in the case report form.

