### Oxygen driven nebuliser regimen

- a. t=0-15 min: 2.5 mg salbutamol by nebulisation, delivered by oxygen at a flow rate of 8L/min
- b. t=15-20 min: Removal of nebuliser mask

- c. t=20-35 min: 2.5 mg salbutamol by nebulisation, delivered by oxygen at a flow rate of 8L/min.

The nebuliser is to continue running for the entire 15 minutes at t=0-15 min and t=20-35 min, even if the bronchodilator medication has dissipated.

Any nasal cannulae oxygen therapy is to be discontinued and nasal prongs removed, during t=0-15 min and t=20-35 min. Oxygen must be restarted at the same flow given prior to nebuliser delivery (i.e. at t=15 the oxygen must be started at the flow delivered at t=0, and at t=35 it must be started again at the flow delivered at t=20 minutes). Note that if the patient was not receiving oxygen before the intervention (was breathing room air) this will continue unless the oxygen saturations drop to <85%. If this occurs the nebuliser mask will be removed, nasal prongs attached and oxygen given. If this does happen it will be recorded in the case report form.

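### Secondary outcome ix pools oxygen-flow increases over two periods, although participants on nasal oxygen at t=0 follow different flow and recording rules by arm in the first

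*Protocol*

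**What the plan says.** **Outcome.** Section 7.D (ix) is a single proportion: "Proportion of patients who required initiation of an increase in the flow of oxygen therapy during the regimen and observation periods". Section 7.A says that outcome variables are compared between the two regimens.

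**Regimen period (t=0-35), participants on nasal oxygen.** Section 6.E.iii sets a different rule for each arm:
- Air arm: "Oxygen therapy is to be continued to be titrated by the un-blinded investigator using nasal cannulae", with the cannulae worn under the nebuliser mask.
- Oxygen arm: "Any nasal cannulae oxygen therapy is to be discontinued and nasal prongs removed, during t=0-15 min and t=20-35 min". In the gap and at the end, "Oxygen must be restarted at the same flow given prior to nebuliser delivery".

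**Regimen period, participants on room air.** In both arms, "this will continue unless the oxygen saturations drop to <85" per cent. If oxygen is then given, both arms record it in the case report form.

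**Recording.** Section 6.E.iv (b) tells the un-blinded investigator, for the regimen period, to "document the time and new oxygen flow (air driven regimen only"). The corresponding instruction for the observation period, Section 6.F.ii (b), carries no such restriction.

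**Observation period (t=35-80).** Section 6.F.i holds flow constant in both arms unless SpO2 falls below 85%. The held flow is the titrated t=35 flow in the air arm and the t=20 flow in the oxygen arm.

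**General role.** Section 4.B.iv (f) lists "Increase oxygen therapy if" SpO2 is below 85%, without distinguishing arm or period.

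**The concern.** A between-arm comparison of flow increases is interpretable when both arms could have had an increase under the same rule and both would have had it written down. After t=35 that is so. Before t=35, for participants already on nasal oxygen, it is not. An air-arm participant may be stepped up at any point in 35 minutes of titration, and the step is documented. An oxygen-arm participant has no cannula flow to raise for most of that time, restarts at a prescribed flow, and is left out of the documentation instruction.

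Pooling the periods mixes this difference in instructions with the comparison that is informative. Section 8.A explains that flow is kept constant after the nebulisers so that rebound can be detected, and Section 2.C (v) hypothesises rebound after oxygen-driven nebulisation. An excess of flow increases in the oxygen arm after t=35 would bear on that hypothesis. Titration steps in the air arm before t=35 could offset it within ix.

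**Working it through.** **1. The plan's own figures.** The protocol states no expected rate, test or power for ix, so there is nothing to reproduce for this outcome. The sample size in Section 10 (82 evaluable for 4 mmHg, SD 5.5, 90% power, alpha 5%) does reproduce: a two-sided t-test needs 40.7, so 41 per arm. It is not in question. From it I take only 90 recruited at 1:1, or 45 per arm.

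**2. Time during which cannula flow can be raised, for a participant on nasal oxygen at t=0.**
- Air: 35 + 45 = 80 minutes.
- Oxygen: 5 (t=15-20) + 45 = 50 minutes.

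These figures do not apply to participants on room air at t=0, who can be started on oxygen at any time in either arm.

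**3. Pooled proportion (all rates assumed).** With regimen rate a and observation rate b, and increases in the two periods independent, pooled = 1 − (1 − a)(1 − b).
- Air, a = 15%, b = 5%: 1 − 0.85 × 0.95 = 19.25%.
- Oxygen, a = 0%, b = 20%: 20%.

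The observation-period difference is 15 points and the pooled difference is 0.75. Without independence, the air figure lies between 15% (complete overlap) and 15 + 5 = 20% (no overlap), so the pooled difference lies between 5 and 0 points.

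The arm-wide rate a equals the share on oxygen at t=0 times the proportion of those stepped up. For example, 50% × 20% = 10%. The protocol gives neither factor.

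**4. Range of consequences (all rates assumed).** 45 per arm, two-sided 5%, normal approximation for two proportions. Observation rate in air is 2%. Regimen rate in oxygen is 0%. Cells show the power to detect an oxygen-arm excess.

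| Air regimen rate | Pooled air | Oxygen 15% | Oxygen 20% | Oxygen 25% |
|---|---|---|---|---|
| 0% (same as observation period alone) | 2.0% | 60.2% | 78.9% | 90.5% |
| 10% | 11.8% | 6.5% | 18.4% | 36.3% |
| 20% | 21.6% | direction reversed | direction reversed | 5.7% |

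If the observation rate is 2% in both arms and the air regimen rate is 20%, pooled ix compares 21.6% with 2%. It would then show a significant excess in the air arm about 83% of the time. The approximation is rough at such low counts (2% of 45 is 0.9 participants), so the table shows direction and order of size only.

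**5. What recording is lost.** Section 6.E.iii sets the oxygen arm's t=35 restart from the t=20 flow, not the t=0 flow. The text therefore allows for a change during the gap, but 6.E.iv (b) does not have it documented in that arm. Flow is recorded at t=0 and again at the end of the second nebuliser (6.F.i), so a net change could be inferred. Its timing, and a temporary increase, could not.

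**6. Two statements on when flow rises in the air arm.** Section 6.E.iii describes continuing titration, and the wash-in target is 88-92% (6.D.ii). Section 4.B.iv (f) names a fall below 85%. For air-arm participants on oxygen these give different meanings to an increase being required, and hence to the event counted in ix.

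**The case against.** **Room-air participants are treated alike.** This stands. The trigger and the case report form entry are the same in both arms. If fewer of them desaturate on oxygen-driven nebulisation, that is a real effect observed under a common rule. A reader might infer that ix as a whole merely measures the protocol's instructions, or that 80 versus 50 minutes describes the arms in general. The text supports neither beyond participants on nasal oxygen at t=0.

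**Rebound is measured elsewhere.** This also stands. Section 8.A defines rebound through SpO2, which is recorded every five minutes to t=80 in both arms, is listed as secondary outcome iv, and is analysed by mixed models (Section 10). No section names ix as the test of hypothesis v. A reader might infer that the trial would miss rebound hypoxaemia. It would not.

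**Titration is part of the air regimen.** More cannula oxygen alongside air-driven nebulisation can fairly be called a consequence of that regimen, so calling the comparison biased against air overstates the case. But the oxygen arm had no equivalent opportunity, so the difference cannot be read as a difference in need.

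**An analysis plan could report by period and define the event.** Largely true: ix names both periods and recorded changes are time-stamped. It cannot fully recover gap changes that the protocol does not ask to have documented.

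**Section 4.B.iv (f) may be only a safety floor.** It does not say that flow rises only below 85%, so it can be read as sitting beneath the titration. The text does not settle this.

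**The rates are constructed.** They are. The calculations show what can happen, not what is expected.

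**Conclusion.** The point holds for participants on nasal oxygen at t=0 and for secondary outcome ix alone. In that group the regimen-period part of ix compares arms under different flow rules and different recording instructions, and pooling lets this distort the one period in which the rule is shared. The size cannot be fixed from the protocol. It depends on the share on oxygen at t=0, how often the air arm is stepped up, and the observation-period rates. If few participants are on oxygen at t=0 or few are stepped up, the effect is small. If the arm-wide step-up rate reaches 10 to 20%, an oxygen-arm excess of the size illustrated would be largely lost or reversed within ix. The primary outcome and the SpO2 assessment of rebound are unaffected. This is an inexpensive correction worth making, not a threat to the trial's main conclusion.

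**What to change.** 1. Report ix in two parts:
   - **t=35-80:** the between-arm comparison, since both arms share one rule. State that the flow held from t=35 is the titrated t=35 flow in the air arm and the t=20 flow in the oxygen arm, so some effect of earlier titration carries over.
   - **t=0-35:** descriptive by arm and by oxygen use at t=0, with the differing rules stated. Section 10 already groups participants by oxygen use immediately before randomisation.
2. Remove the restriction to the air arm from Section 6.E.iv (b), so that any flow change, including at t=15-20, is documented in both arms. This concerns recording only.
3. Reconcile Section 4.B.iv (f) with Section 6.E.iii on when flow is increased in the air arm, so that the event in ix has one meaning. No clinical rule is proposed here.

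The cost is minor rewording of one secondary outcome and one case report form instruction. No measurement is added.
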